### Data collection methods

Data will be collected from people accessing Flourish Australia services and CMO staff at baseline and at follow-up after the intervention period (6 months following the intervention commencement) using repeated cross-sectional sampling. *People accessing services* will complete surveys administered via Computer-Assisted Telephone Interviews (CATI, programmed in REDCap), conducted by trained interviewers from the research team​. Using a CATI script, interviewers will ask participants a structured questionnaire about the support for Living Well Activities they have received, their current Living Well Activities, and perceptions of and satisfaction with support. Telephone interviews allow inclusion of participants who may have literacy or technology access barriers, and this method has been successfully used in similar trials to assess client-reported care receipt [29, 41, 42]​. *Staff* will be invited to complete a self-administered online survey (programmed in REDCap). At each data collection point, an email invitation (from the CMO management) will be sent to all eligible staff at the site with an anonymous survey link and study information statement​. Staff can complete the survey confidentially on their own device, providing information on the support they provide for Living Well Activities. Reminder emails will be sent to improve staff response rates.

### Measures

All survey instruments (for both people accessing supports and CMO staff) were developed specifically for this study. The content of the surveys was informed by prior studies on preventive care in mental health settings [16, 43], and co-developed with stakeholders including CMO managers, staff, people accessing Flourish Australia services and Flourish Australia Community Advisory Council members. This iterative development process involved reviewing the wording and relevance of each question to ensure they were understandable and appropriate for the CMO setting.

#### Primary outcome

The primary outcome for the trial will be the proportion of people accessing Flourish Australia services who report being offered (from the CMO) support to access services or resources for at least one Living Well Activity. Participants will be provided with a definition of the Living Well Activities and asked if *“Anytime within the last six months*,* has your support worker made any suggestions to visit or access services or suggested resources for any living well activities?*” with interviewers recording which Living Well Activity this was for, or “none” as appropriate.

#### Secondary outcomes

Secondary outcomes will be people accessing supports’ receipt and experience of support for Living Well Activities (five outcomes) as well as staff provision of and self-efficacy to provide this support (five outcomes); with questions informed by the Live Well and Flourish Framework.

##### People accessing Flourish Australia services receipt of support for living well activities

At each data collection time point (baseline and follow-up), participants will be asked to report whether they: (i) had a conversation with a support worker that led to identifying at least one Living Well Activity need; (ii) received support to develop plans for at least one Living Well Activity; (iii) made progress about actions/plans for at least one ‘living well activity’ need; and (iv) used at least one support or resource offered for a ‘living well activity’ (e.g. information, links to support groups, telephone support services such as the Get healthy Information and Coaching service, or specialist). Participants will also be asked (v) how satisfied they were with support received for Living Well Activities (rated on a three-point Likert scale: satisfied to dissatisfied).

##### Staff provision of support for living well activities

At both baseline and follow-up, staff will be asked to report the proportion of people they support (0% - not at all; 1–49% - less than half; 50–79% - more than half; 80–100% - most) for whom they have: (i) had conversations with (ii) developed plans or actions (iii) suggested resources/services to connect with (iv) checked back in with about their progress and continued to support needs after an initial conversation; for at least one Living Well Activity. Staff will also be asked to (v) rate their confidence to provide support for at least one Living Well Activity (10-point scale from 1 being ‘not at all confident’ through to 10 being ‘extremely confident’).

#### Current living well activities

Participants will self-report their engagement in each Living Well Activity. *Smoking and Vaping*: Using two items, participants will be asked about current tobacco smoking (including roll your own or cigars) and e-cigarette use (*daily*, *less than daily*, *no)*. *Nutrition (Fruit and Vegetable Intake)*: Daily consumption of fruits and vegetables will be measured by two items asking the number of servings of fruit and the number of servings of vegetables consumed on an average day. *Alcohol Use*: One item will report participants’ frequency of alcohol consumption in the past month *(Never*,* I don’t drink*,* none in the last month*,* once a month*,* 2–4 times a month/once a week*,* 2 to 3 times a week*,* 4 or more times a week)* [44]. *Physical Activity*: A single item will report the number of days in the last week they engaged in at least 30 min of moderate-intensity physical activity [45].

#### Sociodemographic characteristics

*People accessing supports*’ will self-report their age, gender identity, nationality, mental health condition, duration of engagement with the CMO, frequency of accessing support and usual location of support received. *CMO Staff* will self-report their age, gender, cultural identity, highest level of education attained, professional qualifications/background, duration of employment at the CMO, current employment status, current role or position title, number of individuals they typically support in an average week, and the approximate hours of support sessions they conduct per week.

### Process measures

The delivery and uptake of the implementation strategies will be recorded by the research team and champions in project logs, for example, steering group meetings held and attendance, staff completion of training, provision of feedback summaries, provision of project resources, and completion of relevant Flourish Australia tools (preventive health check-in, CANSAS, and IRP). In the follow-up surveys, the uptake of the strategies by staff will be measured e.g., use of the project resources. Staff will also report perceived acceptability, appropriateness and feasibility of the intervention and people supported will report acceptability of the model of care [46]. The project team will record any adaptations made to the intervention and contextual factors in the project logs. Qualitative interviews and/or focus groups with staff and people accessing Flourish Australia supports will be conducted at the intervention to collect additional process measures.

### Sample size

During each round of data collection (baseline and follow-up), approximately 370 people supported by Flourish Australia will be recruited to take part in the survey (185 intervention group, 185 control group). Assuming a baseline prevalence of the primary outcome of 50%, and an intra-class correlation of 0.05, this sample will provide an 80% power to detect an absolute 22.5% difference between the groups, with a type 1 error rate of 5%. Approximately 100 staff will be recruited in each round of data collection.

### Statistical analysis

Analyses will be conducted on an intention-to-treat basis. Characteristics of sites and people accessing supports will be summarised for each group using means and standard deviations (or medians and interquartile ranges) for continuous measures, and counts and percentages for categorical measures. Mixed effects logistic regression models will assess changes over time in the intervention compared to control group for primary and secondary outcomes. Models will include a fixed effect for group, random effect for cluster, and a fixed effect for individual to account for any repeated measures on people accessing support over time. Confounding variables such as age, gender and length of time accessing the CMO will also be adjusted for as fixed effects in the model. The threshold for statistical significance will be alpha = 0.05. Process and other measures will be summarised descriptively.

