## Methods

### Study design and setting

A cluster randomised controlled trial with two parallel groups will be conducted within one large mental health CMO (Flourish Australia). The unit of randomisation will be sites, with 12 sites participating across three regions (Hunter and New England, Queensland, South Australia; as defined by Flourish Australia). In the 2023/2024 financial year, Flourish Australia supported 8,975 people [35]. The type of services provided included support for housing, employment, social opportunities, as well as access to services such as The National Disability Insurance Scheme (NDIS), Headspace and other clinical services. Approximately 36% of the service delivery team are peer workers, using their own mental health lived experience to inform their practice [35].

The study design is depicted in Fig. 1. Supplementary File 1 contains the SPIRIT schedule. After baseline survey data collection from all sites, sites will be randomised (1:1) to either a usual care control condition or a six-month practice change intervention. The intervention will comprise (1) a new model of providing support for Living Well Activities (i.e. preventive care), and (2) implementation strategies to support staff in delivering this care. The intervention will be implemented at the site level, independent of individual participation in data collection. Primary and secondary outcomes regarding receipt of preventive care will be measured through two rounds of independent cross-sectional telephone surveys with people accessing Flourish Australia services (baseline and post-intervention follow-up). Additional secondary outcomes regarding staff provision of care and perspectives of care for Living Well Activities, will be measured through two rounds of cross-sectional online surveys (baseline and post-intervention follow-up).

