#### Recruitment of CMO staff

Approval will be obtained from the Flourish Australia managers at each site. Eligible staff will be contacted via email including an invitation to participate in the study survey, copy of the participant information statement, and an anonymous survey link by CMO administrative staff. Consent is implied by staff submitting a survey response.

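### The stated model gives every individual a fixed effect alongside a fixed group effect, so the group effect cannot be estimated; the listed terms also omit survey round and group-by-round

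*Protocol article*

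**What the plan says.** The Statistical analysis section of the protocol article states the aim first: "Mixed effects logistic regression models will assess changes over time in the intervention compared to control group for primary and secondary outcomes". It then lists the terms: "Models will include a fixed effect for group, random effect for cluster, and a fixed effect for individual", the last of these to allow for repeat measurements on service users over time. The covariates follow: "Confounding variables such as age, gender and length of time accessing the CMO will also be adjusted for as fixed effects in the model". Survey round appears nowhere in the list, and neither does its interaction with group.

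Study design and setting describes the data behind the primary outcome as "two rounds of independent cross-sectional telephone surveys with people accessing Flourish Australia services", once at baseline and once after the intervention. Data collection methods likewise calls the sampling repeated and cross-sectional. Sites are the unit of randomisation: 12 sites, allocated 1:1 after the baseline surveys. The article does not say how many people are expected to answer in both rounds.

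**The concern.** A fixed effect for each individual absorbs everything that is constant within a person, and in a cluster-randomised trial the arm is constant within a person. The model as listed asks for both, so it has no estimable group effect. The reason given for the individual term, occasional repeat respondents, is what a random intercept is for.

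An analyst who finds that the published primary model cannot be fitted must choose another. The Randomisation and blinding section says that this analyst will know the allocation. The obvious replacements (group only, follow-up only, difference in change) do not all estimate the same quantity and do not have the same power. The cost-effectiveness ratio, expressed per percentage point gained, would inherit whichever was chosen.

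**Working it through.** **Inputs.** Sample size section: 370 people per round (185 per arm), 50% baseline prevalence, intra-class correlation 0.05, 22.5-point difference, 80% power, 5% type 1 error (taken as two-sided). Study design and setting: 12 sites, hence 6 per arm. Assumed: each person stays with one site, and baseline prevalence is 50% in both arms.

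**1. The plan's own figure.** People per site per round: 370/12 = 30.8. Design effect: 1 + (30.83 − 1) × 0.05 = 2.49. Effective number per arm: 185/2.49 = 74.2. Power for 50% against 72.5% by the normal approximation is 81.0%, against 80% stated. The sample size statement reproduces, as a comparison of the two arms in a single round.

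**2. Is group estimable beside individual fixed effects?** Let D_i be the indicator for person i. The group variable equals the sum of D_i over everyone in the intervention arm, so it is an exact linear combination of the individual indicators. This was checked by the rank of the design matrix with 12 sites and 31 people per site per round (744 records), for an assumed range of repeat respondents:

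| Repeat respondents per site | Individuals | Rank, individuals only | Adding group | Adding group and round | Adding group, round and group-by-round |
|---|---|---|---|---|---|
| 0 | 744 | 744 | 744 | 744 | 744 |
| 8 | 648 | 648 | 648 | 649 | 650 |
| 15 | 564 | 564 | 564 | 565 | 566 |
| 31 (all) | 372 | 372 | 372 | 373 | 374 |

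Adding group never raises the rank, so its coefficient is not estimable at any overlap. With no overlap the model is saturated: one parameter per record. Adding round and group-by-round makes the interaction estimable only when some people answer twice, and then only from those people (8 × 12 = 96 of 648 individuals in the second row).

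**3. What if the individual term is dropped and the rest of the list is kept?** The group coefficient then pools both rounds. Control: 50%. Intervention: (50 + 72.5)/2 = 61.25%. The difference is 11.25 points, with odds ratio (0.6125/0.3875)/(0.50/0.50) = 1.58. The planned follow-up effect is 22.5 points, with odds ratio 0.725/0.275 = 2.64.

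**4. How much does the choice of replacement matter?** A simulation of site-level summaries (4,000 runs per setting, 31 people per site per round, t test on 6 against 6 sites) used between-round correlations of site effects of 0.5, 0.8 and 1.0. The article gives no such correlation, so this range is an assumption.

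| Analysis | Mean estimate (points) | Power |
|---|---|---|
| Group only, rounds pooled | about 11.3 | 29–34% |
| Follow-up only | about 22.5 | 71–72% |
| Difference in change | about 22.4 | 57–82% |

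The follow-up-only power lies below the 81% of step 1 mainly because a t reference with 10 degrees of freedom replaces the normal one; the analytic t figure is about 74%.

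**The case against.** The strongest reply is that fixed is a slip for random. The term is introduced to handle repeated measures inside a mixed model, which is the job of a random intercept, and a literal fit would expose the collinearity at once. A silently wrong result is therefore unlikely. This is plausible, but the text sets a random effect for site and a fixed effect for individual side by side, so a reader cannot be sure, and the rule as published is still wrong.

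The second reply concerns the missing round terms. The sentence before the list states a difference in change in words, and an article may condense its list of terms. That largely stands. The omission is a supporting point, and the 11-point figure arises only if someone follows the list and disregards that sentence.

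Four stronger readings are tempting but not supported:

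- **Little overlap between rounds.** A reader might take it as given that few people answer twice. Both rounds draw on the same 12 sites and no overlap is stated. The collinearity does not depend on it; the count of about 740 parameters does.
- **An inflated odds ratio.** A reader might predict a specific inflation from individual fixed effects. That needs a different model (with round terms) and a within-person odds ratio, which the article does not give.
- **Anonymous staff surveys.** The staff survey uses "an anonymous survey link by CMO administrative staff", which might seem to make the individual term impossible. But the term's stated purpose is repeat measures on service users.
- **Logistic models for scaled secondary outcomes.** Staff are asked to "rate their confidence to provide support for at least one Living Well Activity (10-point scale" among other graded items. How these are cut or modelled is commonly left to the statistical analysis plan, which is not shown, and no loss of information can be computed without knowing the cut.

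**Conclusion.** The point holds. As written, the model for the primary outcome has no estimable group effect. This follows from the design, on the sole assumption that each person stays in one arm, and does not depend on the overlap between rounds. In the limit of fully independent samples, the individual terms would use up all of about 740 records, and an added group-by-round term would not be estimable either.

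The missing round and group-by-round terms are a lesser inconsistency between the stated target and the listed terms. Their size, 11.25 points instead of 22.5, rests on the sample size section's inputs, equal baseline prevalence, rounds of equal size, and a literal reading of the list without the individual term. Nothing here shows that the stated sample size is wrong on its own inputs.

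**What to change.** Reword the model description as follows:

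- Replace the individual fixed effect with a random intercept for people who can be linked across rounds; omit the term if they cannot be linked.
- List fixed effects for group, survey round and group-by-round, together with the covariates already named.
- Keep the random effect for site. A site-by-round random effect is optional.
- Name the group-by-round contrast, that is, the intervention effect at follow-up, as the primary estimate.

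The cost is a rewording of the analysis section. Design, sample and data collection do not change. The correction should be made before follow-up data are analysed, because the primary analyst will know the allocation.

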### Economic evaluation

The economic evaluation will comprise of (i) a costing analysis, (ii) a cost-consequence analysis using a scorecard approach to present costs in conjunction with the outcomes from the trial, and (iii) cost-effectiveness analysis, where the primary outcome will be incremental cost per percentage point increase in participants reporting receipt of support via an offer to facilitate access to resources Sensitivity analyses will be conducted to assess the impact of plausible variations in key input parameters, such as labour costs, informed by project logs.

Resource use and costs associated with the development and implementation of the model of care and related strategies will be prospectively identified, measured, and valued from a health service delivery perspective, in accordance with the Consolidated Health Economic Evaluation Reporting Standards (CHEERS) 2022 [47]. Data on resource use will be collected by the research team during the intervention period using structured project logs and qualitative interviews/focus groups. Cost categories will include: (1) implementation costs (e.g., materials, labour, and other direct expenses); (2) service delivery costs (e.g., staff time allocated to preventive care activities); and (3) opportunity costs borne by providers and service users. All costs will be reported in local currency and, where applicable, adjusted for inflation using appropriate indices. Costs related solely to research activities, such as data collection, will be excluded from the analysis.

## Discussion

People living with a mental health condition experience a greater burden of chronic disease morbidity and mortality worldwide, contributing to a reduced life expectancy [1]. Current recommendations suggest that mental health services routinely and systematically offer support for health risk factors which contribute to this inequity [5, 7]. An important and growing part of the mental health sector are CMO’s and previous research indicates that although they may be providing some support for health risk factors, there is scope for improvement [12, 13].

There is a need for interventions that assist CMO workers to provide routine and comprehensive care [10, 12, 13]. These interventions should be aligned with existing CMO models of care, which may be achieved through co-development with staff and people accessing services. This protocol describes a cluster-randomised controlled trial aiming to test the effectiveness of a practice change intervention to increase the provision of support for ‘Living Well Activities’ by support workers in a large CMO. This will include the delivery of a model of care, the ‘Live Well and Flourish Framework’, supported by evidence-based implementation strategies. Both the model of care and implementation strategies have been co-developed to ensure appropriateness, acceptability and feasibility within the mental health CMO setting. This protocol and the subsequent trial it describes will strengthen the research regarding effective implementation of interventions assisting CMO workers to support health behaviour change and promote physical and mental wellbeing. Outcomes of the trial will help inform future initiatives for such support in the mental health CMO sector, providing evidence of the cost-effectiveness of this support. These outcomes will inform both future research as well as the direction of practical policy and funding strategies.

## Data Availability

No datasets were generated or analysed during the current study.

## Abbreviations

CMO: Community Managed Organisation
NSW: New South Wales
AAR: Ask, advise, refer
5As: Assess, advise, agree, assist, arrange
NDIS: National Disability Insurance Scheme
SPIRIT: Standard Protocol Items: Recommendations for Interventional Trial
BOTH: Flourish Australia’s Back on Track Health Program
CANSAS: Camberwell Assessment of Need
IRP: Individual Recovery Plan
CATI: Computer-Assisted Telephone Interviews
CHEERS: Consolidated Health Economic Evaluation Reporting Standards
